### Safety outcomes

Safety outcomes will include the occurrence of both common and serious intraoperative or postoperative adverse events. Common adverse events consist of neck pain, dizziness, tinnitus, and mild allergic reactions, which will be evaluated by combining patient complaints with clinical observation. Serious adverse events include respiratory depression, defined as a sustained SpO_2_ of less than 90% or the need for assisted ventilation; anaphylaxis, defined as the development of anaphylactic shock; sinus bradycardia, defined as a heart rate of less than 50 beats per minute; hematoma formation; infection; severe arrhythmias; pneumothorax; and complications related to general or spinal anesthesia.

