### Randomization and blinding

An independent research staff member will generate the randomization sequence using the Sealed Envelope online tool,^1^ with a 1:1 allocation ratio, permuted blocks of 2 and 4, and stratification by age (18–64 and ≥65 years). The allocation results will be stored in sequentially numbered, sealed opaque envelopes. Patients will be randomly assigned to either the SGB group or the control group (*n* = 150 per arm). The anesthesiologists responsible for administering the intervention will be aware of group allocation due to the nature of the procedure but will not be involved in patient recruitment, data collection, or outcome assessment. Patients, surgeons, postoperative care providers, outcome assessors, and the data analyst will remain blinded to group assignments throughout the study. Successful stellate ganglion block in the intervention group will be confirmed by the occurrence of Horner’s syndrome (ptosis, miosis, enophthalmos, conjunctival hyperemia, and facial anhidrosis). Patients will not be informed whether these clinical signs occur, thereby maintaining the integrity of blinding. The schedule for patient enrollment, study interventions, and outcome assessments will adhere to the SPIRIT statement (Table 1).

**Table 1 tab1:** SPIRIT schedule of patient enrolment, study interventions and outcome assessment.

Time point	Study period									
	Enrolment	Allocation	Post-allocation					Close-out	Follow-up	
	Emergency room	15 min Pre-an	Intraoperative	Post-op	24 h Post-op	48 h Post-op	72 h post-op	Discharged	1 month	6 months
Patient enrolment										
Eligibility criteria	**×**									
Written informed consent	**×**									
Demographic data	**×**									
Baseline characteristics	**×**									
Randomization/allocation	**×**									
Study interventions										
SGB		**×**								
Sham SGB		**×**								
Outcome assessment										
CAPS-5 score									**×**	**×**
BAI score					**×**	**×**	**×**			
VAS Sleep score					**×**	**×**	**×**			
NRS Pain score					**×**	**×**	**×**			
HRV			**×**		**×**	**×**				
Recovery time				**×**						
Extubation time				**×**						
RASS score				**×**						
Length of hospital stay								**×**		
Safety Outcomes										
Neck pain			**×**		**×**	**×**	**×**			
Dizziness			**×**		**×**	**×**	**×**			
Tinnitus			**×**		**×**	**×**	**×**			
Dyspnea			**×**		**×**	**×**	**×**			
Anaphylaxis			**×**		**×**	**×**	**×**			
Sinus bradycardia			**×**		**×**	**×**	**×**			

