Hematoma formation			**×**		**×**	**×**	**×**			
Infection			**×**		**×**	**×**	**×**			
Severe arrhythmia			**×**		**×**	**×**	**×**			
Pneumothorax			**×**		**×**	**×**	**×**			
General spinal anesthesia			**×**		**×**	**×**	**×**			

SGB, Stellate Ganglion Block; CAPS-5, the Clinician-Administered PTSD Scale for Diagnostic and Statistical Manual of Mental Disorders (Fifth Edition); BAI, Beck Anxiety Inventory; VAS, Visual Analogue Scale; NRS, Numerical Rating Scale; HRV, Heart Rate Variablity; RASS, Richmond Agitation Sedation Scale; Sinus bradycardia, defined as HR<50 beats/min; Pre-an, Preanesethesia; Post-op, Postoperative; SPIRIT, Standard Protocol Items: Recommendations for Interventional Trials.

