### Study interventions

Patients will receive either a right SGB or a sham procedure 15 min prior to induction of anesthesia. In the SGB group, 5 mL of 0.5% ropivacaine will be injected around and into the stellate ganglion at the level of the C6 anterior tubercle under ultrasound guidance (23). In the control group, 2 mL of preservative-free normal saline will be injected into the deep musculature anterolateral to the anterior tubercle of C6, deliberately avoiding the stellate ganglion. The injection of 2 mL saline into a region other than the stellate ganglion is mainly for evaluating the placebo effects of the study procedures. Apart from the injectate and its site of deposition, all other procedures, including patient preparation, positioning, ultrasound guidance, and needle insertion technique, will be identical in both groups.

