### Anesthesia procedures and perioperative management

All patients enrolled in this trial will undergo general anesthesia. Intraoperative monitoring will include non-invasive blood pressure (NIBP), electrocardiography (ECG), pulse oximetry (SpO_2_), and bispectral index (BIS). Anesthesia will be induced with intravenous propofol (1.5–2.5 mg/kg), combined with sufentanil (0.2–0.4 μg/kg) for analgesia. Rocuronium (0.6–0.9 mg/kg) will then be administered to facilitate muscle relaxation. Following induction, endotracheal intubation will be performed, and tube placement will be confirmed. Mechanical ventilation will be initiated to maintain end-tidal carbon dioxide between 35 and 45 mmHg.

Anesthesia maintenance will consist of continuous infusions of propofol (2–4 mg/kg/h) and remifentanil (0.1–0.2 μg/kg/min), along with 1% sevoflurane. BIS values will be maintained between 40 and 60. Intraoperative hypotension (mean arterial pressure <65 mmHg or a ≥20% decrease from baseline) and bradycardia (heart rate <50 beats/min) will be treated as needed.

All patients will receive 8 mg of ondansetron to prevent postoperative nausea and vomiting. In the postoperative ward, if the VAS pain score exceeds 4, 50 mg of intravenous flurbiprofen axetil will be administered for analgesia.

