### Data collection and monitoring

Patient data will be thoroughly reviewed by the research team using individual electronic medical records. The collected baseline variables will include age (years), sex, body mass index (BMI, kg/m^2^), education level, preoperative medications, comorbidities, American Society of Anesthesiologists (ASA) physical status classification, smoking status, and the time from injury to anesthesia induction, among others. Post-discharge information will be obtained via direct interviews or telephone follow-ups and recorded in the follow-up management system. In addition, major life events such as serious illnesses, accidents, or the death of close family members will also be documented.

All data will be recorded on case report forms (CRFs) and entered into a secure electronic database under the supervision of the principal investigator. An independent Data Monitoring Committee (DMC) will oversee the data collection process throughout the study. Upon completion of data entry, the database will be locked and anonymized datasets will be submitted to an independent statistician for final analysis according to the predefined statistical analysis plan.

Any serious adverse events (SAEs), whether related or unrelated to the study intervention, must be reported immediately to the principal investigator. Appropriate medical measures will be initiated by the perioperative care team to ensure patient safety. In addition, all SAEs will be reported to the DMC within 24 h for evaluation, including assessment of whether protocol modifications or study termination is required.

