In this study, we will perform a right stellate ganglion block under ultrasound guidance. Ultrasound-guided SGB is a safe and effective method (19). The right side was chosen on the basis of functional hemispheric lateralization, as previous studies have demonstrated right-sided dominance of the sympathetic nervous system and neural circuits related to fear and anxiety (23, 28, 29). Unilateral blockade is sufficient to modulate sympathetic activity while minimizing the risk of complications associated with bilateral procedures, such as recurrent laryngeal nerve palsy or phrenic nerve paralysis.

This randomized controlled trial investigates the potential of SGB to prevent PTSD in patients undergoing emergency ocular trauma surgery. Mechanistically, PTSD is characterized by chronic overactivation of the sympathetic nervous system, which promotes excessive consolidation of fear memories, manifesting clinically as recurrent flashbacks and hypervigilance (30, 31). This hyperadrenergic state is thought to be driven by elevated levels of nerve growth factor (NGF), which facilitates sympathetic sprouting and increases systemic norepinephrine (NE). SGB may counteract this process by downregulating NGF and/or NE, thereby disrupting the pathological sympathetic feedback loop and mitigating the development of PTSD-related symptoms (32). Our previous preclinical study further supports this hypothesis, demonstrating that SGB attenuated conditioned fear memory formation in mice by inhibiting noradrenergic projections from the locus coeruleus to the basolateral amygdala (20).

Visual deprivation resulting from ocular trauma may enhance emotional sensitivity and facilitate the encoding of fear-related memories, possibly through heightened activation of the amygdala, a key brain region involved in emotional processing and memory consolidation (33, 34). SGB may exert its preventive effect on PTSD by inhibiting sympathetic outflow at the stellate ganglion level, thereby attenuating excessive amygdala activation and potentially disrupting the early consolidation of fear memories following trauma (20, 31).

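### Table 1 schedules no safety check between injection and induction or at the Post-op assessment, and places complaint-based symptoms under general anesthesia, so transient non-serious block effects may be under-recorded

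*Protocol article*

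**What the plan says.** All references are to the protocol article.

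- *Safety outcomes* sets the window: "Safety outcomes will include the occurrence of both common and serious intraoperative or postoperative adverse events". Neck pain, dizziness, tinnitus and mild allergic reactions are the common events, "which will be evaluated by combining patient complaints with clinical observation". Respiratory depression, anaphylaxis, bradycardia, hematoma, infection, severe arrhythmia, pneumothorax and anesthesia complications are classed as serious.
- *Study interventions* fixes the time of the injection: "Patients will receive either a right SGB or a sham procedure 15 min prior to induction of anesthesia".
- *Anesthesia procedures and perioperative management* adds: "All patients enrolled in this trial will undergo general anesthesia".
- *Table 1* (SPIRIT schedule) has 11 safety rows, all with the same four marks: Intraoperative, 24 h, 48 h and 72 h.
- *Randomization and blinding* says that the anesthesiologists giving the block know the allocation and "will not be involved in patient recruitment, data collection, or outcome assessment".
- *Data collection and monitoring* sets a separate route for serious events: "Any serious adverse events (SAEs), whether related or unrelated to the study intervention, must be reported immediately to the principal investigator". These also go to the monitoring committee within 24 h.

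**The concern.** Safety is a stated aim of the trial, next to efficacy. A single injection has its transient effects soon after it is given. The interval before induction is the one period in which those effects can be seen, and described by the patient, without general anesthesia on top. Early recovery is the next. The schedule has no safety mark in either, and it spends one of its four marks for symptoms at a time when the patient cannot speak.

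The arms differ in injectate, volume and site (5 mL of 0.5% ropivacaine at the ganglion against 2 mL of saline in muscle away from it), so short-lived effects may differ by arm. If such events are recorded with the same probability *s* in both arms, the expected recorded risk difference is *s* × (p_SGB − p_sham), which shrinks as *s* falls. Under-recording would then make the active block look closer to sham than it is.

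**Working it through.** The plan gives no figure on this point to reproduce. The check is a count of marks in Table 1, set beside the text.

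**Step 1. Are the columns read correctly?** The table was extracted from PDF, so rows with known timing serve as a control. HRV falls at Intraoperative, 24 h and 48 h, as *Secondary outcomes* states. BAI, sleep and pain scores fall at 24, 48 and 72 h, also as stated. SGB and sham fall at the pre-anesthesia column, as *Study interventions* states. The alignment can be trusted.

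**Step 2. Count of safety marks.** The rows are neck pain, dizziness, tinnitus, dyspnea, anaphylaxis, sinus bradycardia, hematoma, infection, severe arrhythmia, pneumothorax and general spinal anesthesia (11 rows).

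| Table 1 column | Safety rows marked | What else is marked there |
|---|---|---|
| 15 min Pre-an | 0 of 11 | SGB, sham SGB |
| Intraoperative | 11 of 11 | HRV |
| Post-op | 0 of 11 | Recovery time, extubation time, RASS |
| 24 h | 11 of 11 | BAI, sleep, pain, HRV |
| 48 h | 11 of 11 | BAI, sleep, pain, HRV |
| 72 h | 11 of 11 | BAI, sleep, pain |

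Post-op is therefore an existing assessment point that safety does not use.

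**Step 3. Symptoms that need a report.** Three of the rows (neck pain, dizziness, tinnitus) are tied to patient complaints in *Safety outcomes*. They carry 3 × 4 = 12 marks. Three of the 12 are intraoperative, under general anesthesia. The other 9 are at 24, 48 and 72 h. Taking 24 h as counted from the end of surgery, the first check at which a patient can answer comes at 15 min + duration of anesthesia and surgery + 24 h after the injection, so more than 24 h after it.

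**Step 4. Text against table.**

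| Item | *Safety outcomes* | Table 1 |
|---|---|---|
| Injection to induction | Not named (intraoperative or postoperative only) | No safety mark |
| Immediate postoperative period | Covered by the word postoperative | No safety mark |
| Breathing event | Respiratory depression, defined by SpO2 or assisted ventilation | Dyspnea, a symptom |
| Mild allergic reactions | Listed | No row; only anaphylaxis |
| Anesthesia event | General or spinal anesthesia complications | General spinal anesthesia |

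The pre-induction gap is in both places. The Post-op gap is in the table only, so it is a mismatch with the text.

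**Step 5. Who records before induction?** The operator is kept out of data collection, and the article names no one else for that interval.

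**The case against.** The strongest reply is that little of importance can be lost.

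- **Serious events.** A reader might infer that early block complications would be missed. The documents do not support this. Most of the dangerous ones are classed as serious, and serious events must be reported at once with no time window. This part of the reply stands in full.
- **Later recall and charting.** The 24 h check may ask about symptoms since the procedure, data are also reviewed from electronic medical records, and the operator's exclusion from trial data collection does not prevent clinical charting. The Intraoperative column might also be meant to include theatre time before induction. All this is possible, so it cannot be said that transient events are unrecordable. None of it is stated, and recall after more than a day, with an anesthetic in between, is a weak substitute for asking at the time.
- **Condensed article.** The full protocol or case report form may say when recording starts. That would excuse an absent detail. Table 1, however, is an explicit schedule with marks, and it disagrees with its own text.
- **Nerve palsies.** A reader might infer that the safety list omits complications the protocol itself attributes to this block. The *Discussion* does mention complications "such as recurrent laryngeal nerve palsy or phrenic nerve paralysis", but it ties them to bilateral procedures and gives them as a reason for choosing a unilateral block. There is no contradiction.
- **Spinal anesthesia.** A reader might see a conflict with general anesthesia for all. The table row sits among adverse events and may mean unintended spread of the injectate. It is unclear wording, no more.
- **Blinding.** Having the operator record events would let ascertainment differ between arms. This stands, and it shapes the fix.

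**Conclusion.** The point holds in a limited form. The schedule has no safety mark at the time of the block (0 of 11 rows) or at the existing Post-op assessment (0 of 11), and it places three complaint-based symptoms under general anesthesia, so the first scheduled opportunity to report them is 24 h after surgery. The consequence is a risk of under-recording transient, non-serious effects before induction and in early recovery.

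It is tempting to turn this into a number of lost events. The documents give neither a rate for such effects nor the share that would go uncharted and unrecalled, so no figure is justified.

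The conclusion rests on two assumptions: that the patient can report symptoms between injection and induction (the article describes no sedation before the block), and that Intraoperative means after induction. The primary outcome, its analysis and the sample size are untouched. The correction is worth making because safety is a stated aim and the remedy is cheap.

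**What to change.** 1. State in *Safety outcomes* that adverse-event recording starts at needle insertion.
2. In Table 1, mark the safety rows at the pre-anesthesia and Post-op columns.
3. Limit the Intraoperative marks to signs that can be observed in an anesthetized patient; remove them for neck pain, dizziness, tinnitus and, if it stays as a symptom, dyspnea.
4. Name who asks. Pre-induction and Post-op symptoms should be asked with the same questions in both arms, by existing blinded staff where possible. Any entry by the unblinded operator should be kept separate, flagged as such and withheld from the blinded assessors.
5. Reconcile the terms: respiratory depression or dyspnea, a row for mild allergic reactions, and one clear name for the anesthesia-related event.

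The cost is a table amendment and a little more case report form work at two time points that already exist, with no added visit. The remaining downside is that some pre-induction entries may still come from unblinded staff; flagging them allows the safety comparison to be shown with and without them.

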### Randomization and blinding

An independent research staff member will generate the randomization sequence using the Sealed Envelope online tool,^1^ with a 1:1 allocation ratio, permuted blocks of 2 and 4, and stratification by age (18–64 and ≥65 years). The allocation results will be stored in sequentially numbered, sealed opaque envelopes. Patients will be randomly assigned to either the SGB group or the control group (*n* = 150 per arm). The anesthesiologists responsible for administering the intervention will be aware of group allocation due to the nature of the procedure but will not be involved in patient recruitment, data collection, or outcome assessment. Patients, surgeons, postoperative care providers, outcome assessors, and the data analyst will remain blinded to group assignments throughout the study. Successful stellate ganglion block in the intervention group will be confirmed by the occurrence of Horner’s syndrome (ptosis, miosis, enophthalmos, conjunctival hyperemia, and facial anhidrosis). Patients will not be informed whether these clinical signs occur, thereby maintaining the integrity of blinding. The schedule for patient enrollment, study interventions, and outcome assessments will adhere to the SPIRIT statement (Table 1).

**Table 1 tab1:** SPIRIT schedule of patient enrolment, study interventions and outcome assessment.

Time point	Study period									
	Enrolment	Allocation	Post-allocation					Close-out	Follow-up	
	Emergency room	15 min Pre-an	Intraoperative	Post-op	24 h Post-op	48 h Post-op	72 h post-op	Discharged	1 month	6 months
Patient enrolment										
Eligibility criteria	**×**									
Written informed consent	**×**									
Demographic data	**×**									
Baseline characteristics	**×**									
Randomization/allocation	**×**									
Study interventions										
SGB		**×**								
Sham SGB		**×**								
Outcome assessment										
CAPS-5 score									**×**	**×**
BAI score					**×**	**×**	**×**			
VAS Sleep score					**×**	**×**	**×**			
NRS Pain score					**×**	**×**	**×**			
HRV			**×**		**×**	**×**				
Recovery time				**×**						
Extubation time				**×**						
RASS score				**×**						
Length of hospital stay								**×**		
Safety Outcomes										
Neck pain			**×**		**×**	**×**	**×**			
Dizziness			**×**		**×**	**×**	**×**			
Tinnitus			**×**		**×**	**×**	**×**			
Dyspnea			**×**		**×**	**×**	**×**			
Anaphylaxis			**×**		**×**	**×**	**×**			
Sinus bradycardia			**×**		**×**	**×**	**×**			
Hematoma formation			**×**		**×**	**×**	**×**			
Infection			**×**		**×**	**×**	**×**			
Severe arrhythmia			**×**		**×**	**×**	**×**			
Pneumothorax			**×**		**×**	**×**	**×**			
General spinal anesthesia			**×**		**×**	**×**	**×**			

SGB, Stellate Ganglion Block; CAPS-5, the Clinician-Administered PTSD Scale for Diagnostic and Statistical Manual of Mental Disorders (Fifth Edition); BAI, Beck Anxiety Inventory; VAS, Visual Analogue Scale; NRS, Numerical Rating Scale; HRV, Heart Rate Variablity; RASS, Richmond Agitation Sedation Scale; Sinus bradycardia, defined as HR<50 beats/min; Pre-an, Preanesethesia; Post-op, Postoperative; SPIRIT, Standard Protocol Items: Recommendations for Interventional Trials.

### Study interventions

Patients will receive either a right SGB or a sham procedure 15 min prior to induction of anesthesia. In the SGB group, 5 mL of 0.5% ropivacaine will be injected around and into the stellate ganglion at the level of the C6 anterior tubercle under ultrasound guidance (23). In the control group, 2 mL of preservative-free normal saline will be injected into the deep musculature anterolateral to the anterior tubercle of C6, deliberately avoiding the stellate ganglion. The injection of 2 mL saline into a region other than the stellate ganglion is mainly for evaluating the placebo effects of the study procedures. Apart from the injectate and its site of deposition, all other procedures, including patient preparation, positioning, ultrasound guidance, and needle insertion technique, will be identical in both groups.

### Intervention implementation process

Patients will be placed in the supine position with the head slightly rotated to the left. A thin pillow will be positioned under the shoulders to slightly extend the neck and optimize exposure. At the level of the C6 vertebra, between the trachea and the carotid artery, a high-frequency linear ultrasound probe will be used to gently displace the carotid artery laterally, allowing visualization of the transverse process of C6 with its prominent anterior and posterior tubercles, as well as the longus colli muscle located superficial to the transverse process and covered by the prevertebral fascia. Using an in-plane technique, the needle will be advanced under real-time ultrasound guidance. It will traverse the sternocleidomastoid and anterior scalene muscles, then pass into the space between the anterior tubercle of the C6 transverse process and the internal jugular vein, reaching the anterior surface of the longus colli muscle beneath the prevertebral fascia. If no blood is aspirated, the study solution will be injected. All procedures will be performed under sterile conditions by an experienced anesthesiologist, using real-time ultrasound guidance. The presence of ipsilateral Horner’s syndrome is considered an indicator of successful blockade.

